**4. [Research method and period]**

① Research implementation period

From November 1, 2017 to March 31, 2021.

② Information on drugs used

Name: Tsumura Yokukansan (Product number: 054)

Route of administration, dosage and administration: Oral, 1 packet (2.5 g) at a time

Dosage form: Extract granules

③ Research subjects

Patients aged 20 to 60 years who undergo breast cancer surgery at Niigata University Medical and Dental Hospital or Niigata Prefectural Cancer Center Niigata Hospital and undergo total mastectomy and sentinel lymph node biopsy, or partial mastectomy and sentinel lymph node biopsy (Details will be described later).

④ Research method

Multicenter / Open Label / Superiority test by forced random sampling

[1] A pre-treatment questionnaire survey will be conducted on all subjects, and the age, BMI, surgical history, and general status (American Society of Anesthesiologists-Physical Status: ASA-PS, ECOG-PS) will be recorded in advance. Also, before taking the study drug, record the measurement of amylase in saliva, the Hospital anxiety and depression scale (HADS), and the State Trait Anxiety Inventory (STAI).

[2] Subjects are assigned to two groups, one with yokukansan (intervention) and the other without (control), according to the results of randomization. The intervention group should be given 1 packet (2.5 g) of TSUMURA Yokukansan before sleep on the day before surgery and 1 packet (2.5 g) 2 hours before entering the operating room on the day of surgery. For the purpose of maintaining the same quality between the two groups, a forced allocation algorithm is created, and if a bias is confirmed between the groups, forced allocation is performed based on age, surgical history, etc.

[3] Subjects in the intervention group take 1 packet of yokukansan orally 2 hours before entering the operating room on the day of surgery, and then all participants are measured salivary amylase in the operating room. Anesthetized by general anesthesia in the operating room and undergo total or partial mastectomy and sentinel lymph node biopsy

[4] Record salivary amylase measurements, HADS, STAI, visual analog scale of pain: VAS, QOR (Quality of recovery), and the presence or absence of analgesic use 24 hours after surgery.

| 24-hour before surgery | Salivary amylase  HADS STAI |
| --- | --- |
| Just before surgery | Salivary amylase |

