| 24-hour after surgery | Salivary amylase  HADS STAI  Visual analog scale for postoperative pain  QOR  Rescue analgesics usage |

※The allowable range is ± 12 hours before and 24 hours after surgery.

⑤ Sample size

In this study, we plan to perform Bayesian analysis. In this method, the posterior probability of the response rate is calculated by an interim analysis, and the calculated posterior probability is monitored. If it is judged that the effect is not as good as that of untreated, the test should be discontinued. Is planned. In addition, since the posterior predictive distribution is obtained based on the data obtained from the interim analysis, it is possible to judge whether the additional data follows the distribution, and it is possible to save the number of cases by performing this procedure. Is known to be. As an interim analysis, an exploratory analysis will be performed when 20 cases in a group are reached based on reference [1]. Recalculate the required number of cases based on the results of the interim analysis. Regarding the design of the number of cases, referring to the previous study, 1-β was 80%, the significance level was 0.05, and the success rate of the intervention group (yokukansan was expected to be taken preoperatively and preoperatively: impression at the outpatient clinic of pain clinic) is set to 75%. About 40 cases are expected in each group. The clinically meaningful difference is defined as σ = 0.3.

[1]Young-Chang Arai, et al, Evidence based Complementaly and Alternative Medicine.2014; ID965045

⑥ Study endpoints

Primary endpoint: Salivary amylase level

Secondary endpoint: HADS STAI QOR Pain VAS

⑦ Analysis method

Statistical analysis methods are planned to be performed by the maximum likelihood estimation method and the Bayesian statistical method. All analysis is performed by a person in charge of analysis different from that of the principal investigator.

For maximum likelihood estimation methods, t-tests that do not correspond to continuous variables, Fisher's exact test for scale classification, and Mann-Whitney U test for continuous variables or ordinal variables that do not follow a normal distribution such as VAS. A test will be used to determine P <0.05 as significant.

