For Bayesian statistics, the difference between two independent groups is estimated for the primary endpoint. A pre-analysis will be conducted based on the uniform distribution obtained in the exploratory test and the data of 20 subjects, and the obtained distribution will be used as the prior distribution to generate and verify the posterior distribution using the data of 40 subjects in each group.

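### Allocation may be forced on age and surgical history, yet no named analysis includes them; to the extent that forcing is used and the factors are prognostic, the unadjusted t-test is conservative and gives up power

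*Protocol*

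**What the plan says.** Protocol section 4 ④ [2] assigns patients by randomisation and adds a corrective step: "if a bias is confirmed between the groups, forced allocation is performed based on age, surgical history, etc". It gives no algorithm, imbalance threshold or assignment probability, and the factor list is left open. Section 4 ④ [1] has the two named factors collected on every patient before treatment: "the age, BMI, surgical history, and general status (American Society of Anesthesiologists-Physical Status: ASA-PS, ECOG-PS) will be recorded in advance".

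Section 4 ⑦ names the frequentist analyses as "t-tests that do not correspond to continuous variables, Fisher's exact test for scale classification, and Mann-Whitney U test for continuous variables or ordinal variables", judged at P < 0.05. For the Bayesian part, "the difference between two independent groups is estimated for the primary endpoint". Neither part mentions age, surgical history or any other allocation factor.

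**The concern.** Balancing a prognostic factor between the arms removes that factor's contribution to the true variance of the treatment difference. An unpaired t-test does not know this. It leaves the factor's variance in the standard error, so the test behaves as if assignment had been simple randomisation. Two things follow when forcing is used and the factors matter. The true type I error falls below the stated 0.05, and the balance that the allocation bought is only partly turned into power. With about 40 patients per group that power is worth having, and the data needed to recover it are already collected.

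This is a matter of the allocation factors only. Adjusting for baseline amylase, HADS or STAI, or for hospital or type of operation, is a separate question, because the allocation rule does not name those.

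**Working it through.** **Inputs from the protocol (section 4 ⑤).** "1-β was 80%, the significance level was 0.05"; "About 40 cases are expected in each group"; intervention success rate 75%; "The clinically meaningful difference is defined as σ = 0.3".

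**Inputs that are assumed.** A two-sided test; R², the share of outcome variance explained by the allocation factors together; the forcing rule; the coding of the factors; the standardised effect. The protocol gives none of these.

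**1. The plan's own sample size.** Read 0.3 as a difference in success rates, so control is 75% − 30% = 45% (an assumption), with mean rate 0.60:

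n = [1.96·√(2·0.60·0.40) + 0.842·√(0.75·0.25 + 0.45·0.55)]² / 0.3² = (1.358 + 0.555)² / 0.09 ≈ 40.7, so 41 per group.

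This reproduces the stated figure. Read as a standardised mean difference, 0.3 would need 175 per group, which does not. The protocol therefore gives no effect size for amylase as a continuous measure. For the power comparison, the effect giving 80% power at 40 per group was used: d = 0.634, since 0.634·√20 = 2.835 and 2.835 − 1.991 = 0.844, for which Φ = 0.80.

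**2. Size of the unadjusted test under perfect balance.** The true standard error shrinks by √(1 − R²) and the reported one does not, so size = 2·[1 − Φ(1.96/√(1 − R²))]:

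- R² = 0: 0.050
- R² = 0.10: 1.96/0.949 = 2.066, size 0.039
- R² = 0.20: 1.96/0.894 = 2.191, size 0.028
- R² = 0.30: size 0.019

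**3. Size under less complete forcing.** Simulation of 20,000 trials of 80 patients, with a three-level age factor and a two-level surgical-history factor. The Monte Carlo standard error near 0.05 is √(0.05·0.95/20,000) = 0.0015. Size of the unadjusted t-test at nominal 0.05:

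| Allocation | R² = 0 | 0.05 | 0.10 | 0.20 | 0.30 |
|---|---|---|---|---|---|
| Simple (forcing never triggered) | 0.052 | 0.049 | 0.050 | 0.048 | 0.049 |
| Forced once a factor level is out of balance by 4 or more | 0.051 | 0.049 | 0.039 | 0.035 | 0.025 |
| 80/20 biased-coin minimisation | 0.051 | 0.045 | 0.041 | 0.031 | 0.022 |
| Deterministic minimisation | 0.051 | 0.045 | 0.040 | 0.028 | 0.019 |

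The second row is nearest to the protocol's conditional wording. A separate simulation (6,000 trials per cell, deterministic minimisation on two binary factors) gave 0.038 at R² = 0.10 and 0.027 at 0.20. With the factors in a linear model, size in the 20,000-trial runs stayed between 0.047 and 0.053 in every scheme.

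**4. Power, unadjusted vs adjusted.** By formula, with variance scaled by 1 − R² and 76 degrees of freedom, adjusted power at d = 0.634 is 0.839 at R² = 0.10 and 0.879 at 0.20. From the 20,000-trial simulation (effect 0.63 SD):

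| Allocation | R² = 0 | 0.10 | 0.20 |
|---|---|---|---|
| Simple | 0.787 vs 0.772 | 0.791 vs 0.819 | 0.787 vs 0.857 |
| Forced at imbalance of 4 or more | 0.795 vs 0.791 | 0.803 vs 0.832 | 0.815 vs 0.871 |
| 80/20 minimisation | 0.798 vs 0.796 | 0.805 vs 0.835 | 0.817 vs 0.875 |

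The gain is about 3 points at R² = 0.10 and about 6 at R² = 0.20. It does not depend on forcing having happened.

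**5. The Bayesian interval.** Section 4 ⑦ takes a distribution built with 20 subjects, which "will be used as the prior distribution to generate and verify the posterior distribution using the data of 40 subjects in each group". It does not say whether the 20 are among the 40. If 20 per group are counted twice, the mean gives those 20 weight 2 and the other 20 weight 1. Its true variance is (20·4 + 20·1)/60² = 1/36 of the outcome variance, against a claimed 1/60. The ratio of standard errors is √(60/36) = 1.29, and non-coverage of a nominal 95% interval is 2·[1 − Φ(1.96/1.29)] ≈ 0.13. If 20 in total are reused (10 per group), the variance ratio is (70/2500)/(1/50) = 1.4 and non-coverage is about 0.10. Perfect balance would offset this only at R² = 1 − 36/60 = 0.40, or 1 − 1/1.4 ≈ 0.29. The two effects pull in opposite directions.

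**The case against.** Several points against this are sound, and they set its limits.

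- **Forcing is conditional.** A reader might infer that allocation is always forced and that the reported P values are therefore too conservative. The text forces only when an imbalance is confirmed. If that never happens, the t-test keeps its level.
- **Prognostic strength is unknown.** No figure links age or surgical history to amylase or any other endpoint, and eligibility restricts age to 20 to 60. At R² = 0.05 the size distortion is slight.
- **The error is on the safe side.** Conservatism does not create false positives.
- **Intervals.** A reader might also infer that the trial's intervals are too wide. Section 4 ⑦ names no confidence interval, and the direction for the Bayesian interval is unsettled because of the possible reuse of interim patients.
- **Only the t-test was examined.** If amylase is skewed, section 4 ⑦ would move it to the Mann-Whitney test, for which no size figure is given here.
- **The rule itself is undefined.** In an open-label trial an unspecified forcing step could admit selection bias. Adjustment does not cure that, and its effect need not be conservative.
- **The SAP is not shown**, and comparing independent groups does not by itself exclude covariates.

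The mismatch remains. The protocol does not leave the frequentist analysis open: it names particular unadjusted tests after setting up allocation on named factors. The power gain also holds when forcing is rare.

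**Conclusion.** The point holds in conditional form. The protocol allows forcing on age and surgical history and leaves both out of every analysis it names. To the extent that forcing is used and the factors are prognostic, the unadjusted t-test has a true size of about 0.04 at R² = 0.10 and 0.027 to 0.035 at R² = 0.20. The power given up is about 3 and 6 points respectively. These figures rest on assumed R², forcing rules, factor codings and an effect of about 0.63 SD at 40 per group. They assume no selection bias from the forcing step. The documents do not support a claim that every P value is too conservative, or any claim about the direction of the Bayesian interval. This is a worthwhile improvement at almost no cost, and it does not show that the planned tests would mislead in favour of the treatment.

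**What to change.** First state the forced-allocation algorithm and close its factor list, since the covariates follow from it. Then, in section 4 ⑦:

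- Make the primary frequentist analysis of salivary amylase (log-transformed if skewed) a linear model with treatment plus whichever factors the algorithm actually uses: age, surgical history and anything else brought in under the open-ended list.
- Use the same covariates in the Bayesian model of the treatment difference and in the analyses of HADS, STAI and QOR.
- For pain VAS use a rank-based or proportional-odds model with those factors.
- Keep the unadjusted tests as a sensitivity analysis.

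The cost is a change of wording and about two degrees of freedom (age as continuous, surgical history as yes/no), more if further factors are used. Age and surgical history need no new data. If the factors turn out not to be prognostic, the power loss is negligible under forcing (0.798 to 0.796 with 80/20 minimisation). It is at most 1.5 points in the runs above (0.787 to 0.772, with three covariate terms and forcing never triggered).

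### Amylase, HADS and STAI have a pre-dose baseline on every patient, but the planned comparisons make no use of it and so give up precision on these three endpoints

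*Protocol*

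**What the plan says.** All references are to Protocol section 4.

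- **Baseline.** Research method, step 1, covers all subjects: "before taking the study drug, record the measurement of amylase in saliva", together with HADS and STAI. Age, BMI, surgical history and status scores are also recorded in advance.
- **Follow-up.** The schedule repeats amylase just before surgery, and repeats amylase, HADS and STAI 24 hours after surgery. QOR and pain VAS appear only at 24 hours after surgery.
- **Endpoints.** "Primary endpoint: Salivary amylase level" and "Secondary endpoint: HADS STAI QOR Pain VAS".
- **Frequentist analysis.** "t-tests that do not correspond to continuous variables", which reads as a mistranslation of unpaired t-tests; Fisher's exact test for categories; and the Mann-Whitney U test for ordinal or non-normal variables.
- **Bayesian analysis.** "For Bayesian statistics, the difference between two independent groups is estimated for the primary endpoint". No covariate is named.
- **Allocation.** Research method, step 2, lets age and surgical history, among other unnamed factors, steer a forced allocation if the groups look unbalanced.

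Nowhere does the protocol give the baseline value, age or surgical history a role in a between-group comparison. It also does not say whether the tests use post-treatment values or changes from baseline.

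**The concern.** The primary endpoint and two of the four secondary endpoints have a measurement of the same quantity before dosing. An unpaired test on post-treatment values leaves the variation that baseline could explain in the error term. It also lets the correlated part of any chance baseline difference into the estimate. With 40 per group that chance difference has a standard error of √(2/40) = 0.22 SD, so it is not negligible.

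At stake is power and interval width in a small trial. The protocol already worries about imbalance, since it provides for forced allocation, but then leaves the factors it names for that purpose out of the analysis.

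This is more than detail left to a statistical analysis plan. The protocol names specific tests without covariates, and a later plan that used ANCOVA as the main analysis would depart from it.

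**Working it through.** **Inputs from Protocol section 4.** "the significance level was 0.05" (sidedness not stated; two-sided assumed); power 80%; intervention success rate 75%; "The clinically meaningful difference is defined as σ = 0.3"; "About 40 cases are expected in each group".

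**Assumed.** Baseline-outcome correlation r from 0.2 to 0.7, because the protocol gives none. A 0.5 SD difference is used for illustration only. A 0.3 SD difference is one possible reading of the protocol's 0.3.

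**Step 1: the plan's own figure.** Read the 0.3 as a difference in success rates, so that control is 75% − 30% = 45% (not stated in the protocol). With pooled variance,

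n = [1.960·√(2·0.60·0.40) + 0.842·√(0.75·0.25 + 0.45·0.55)]² / 0.30² = 40.7, so 41 per group.

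This agrees with about 40. Read as a standardised difference, n = 2(1.960 + 0.842)²/0.3² = 174.4, so 175 per group, which does not agree. The stated size therefore rests on comparing proportions without covariates. It says nothing about precision on the amylase scale, so the effects below are expressed in SD units.

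**Step 2: if post-treatment values are compared.** ANCOVA multiplies the error variance by 1 − r². Forty per group is then worth 40/(1 − r²) unadjusted patients per group. The difference detectable with 80% power is 0.634·√(1 − r²) SD, where 0.634 SD is the unadjusted figure at 40 per group. Power is from the noncentral t distribution with the standardised difference divided by √(1 − r²).

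| r | Variance cut | 40 per group worth | Detectable difference | Power at 0.5 SD | Power at 0.3 SD |
|---|---|---|---|---|---|
| no adjustment | – | 40 | 0.634 SD | 60% | 26% |
| 0.2 | 4% | 42 | 0.621 SD | 62% | 27% |
| 0.3 | 9% | 44 | 0.605 SD | 64% | 28% |
| 0.5 | 25% | 53 | 0.549 SD | 72% | 33% |
| 0.7 | 49% | 78 | 0.453 SD | 87% | 46% |

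The degree of freedom spent on the baseline term (78 to 77) does not change these power figures at the precision shown.

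**Step 3: if change scores are compared.** With equal SDs at the two times, the variance of a change is 2(1 − r) times that of a single value. The saving from ANCOVA is then

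1 − (1 − r²)/[2(1 − r)] = (1 − r)/2,

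which is 40%, 35%, 25% and 15% at r = 0.2, 0.3, 0.5 and 0.7. The pattern reverses: the saving is largest where r is low. On either reading ANCOVA is at least as precise, apart from the degree of freedom.

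**Step 4: scope.** Same-measure baselines exist for amylase, HADS and STAI. QOR and pain VAS have none, so none of these figures applies to them.

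**The case against.** The strongest case on the other side has five parts.

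1. **Outcome form.** The tests are named, but the quantity tested is not. An unpaired t-test on change scores fits the wording as well as one on post-treatment values. This stands against quoting the step 2 figures alone, and in particular against presenting the rise from 60% to 87% as the expected gain. It does not remove the point, because step 3 still shows a saving.
2. **Unknown correlation.** Amylase may be noisy, and the protocol allows a 12-hour window around the measurements. At r of 0.2 the gain is under 2 percentage points at 0.5 SD (59.8% to 61.6%) if post-treatment values are compared. This stands: for the primary endpoint the gain could be modest.
3. **Effect size.** The protocol does not state 0.5 SD. At 0.3 SD adjustment leaves power below 50% throughout the range, so it does not rescue a trial of this size. This also stands.
4. **No error of validity.** A reader might infer that the unadjusted tests are biased or invalid. The protocol does not support that: under proper randomisation they are unbiased, and only efficiency is lost. Whether forced allocation respects proper randomisation is a separate question, and the factors it names are age and surgical history, not baseline amylase, HADS or STAI.
5. **Room for a later plan.** Covariates are often left to a statistical analysis plan, and the Bayesian sentence does not expressly exclude one. This carries some weight for the Bayesian model, but little for the frequentist analysis, where the tests themselves are fixed.

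**Conclusion.** The point holds as a loss of efficiency on amylase, HADS and STAI. A reader might extend it to all primary and secondary comparisons, but QOR and pain VAS have no baseline of their own, so the protocol does not support that.

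The size cannot be fixed from the protocol. For r between 0.2 and 0.7, the avoidable share of error variance runs from 4% to 49% if post-treatment values are compared, and from 40% down to 15% if change scores are compared with equal SDs. The power figures further assume 40 analysed patients per group, two-sided 5% tests and approximately normal errors. It is worth correcting because the remedy uses data already scheduled for collection, but it does not invalidate the planned tests.

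**What to change.** - **Main analysis.** For amylase, HADS and STAI, replace the unpaired comparison with a linear model (ANCOVA) of the post-dose value on group and the pre-dose value of the same measure. Report the adjusted difference with a 95% confidence interval. Amylase has two post-dose readings, so the sentence must say which one is meant.
- **Bayesian model.** Add the same baseline term to the amylase model, including the 20-case analysis that supplies the prior, so that prior and final analysis estimate the same quantity.
- **Other covariates.** Add age and surgical history, the two named factors that may steer forced allocation. Fix the list before outcome data are seen; the protocol's open-ended wording cannot be entered in a model as it stands.
- **Scale.** Use log amylase only if this is chosen in advance because of skewness. The protocol gives no data on the distribution.
- **Sensitivity.** Keep the t-test or Mann-Whitney test as a sensitivity analysis. QOR and pain VAS can stay as planned.

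**Cost.** One degree of freedom per covariate, slightly more analysis work, and revised wording for both the interim and final analyses. No extra patients or measurements are needed.

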**3. [Purpose and significance of research]**

It is known that excessive perioperative anxiety causes an increase in blood pressure and tachycardia. On the other hand, reducing excessive perioperative anxiety is known to be shortened the postoperative course and hospitalization period and postoperative pain. Benzodiazepine anxiolytics have traditionally been used as pre-anesthetic medications to reduce perioperative anxiety [1], but benzodiazepines can cause excessive sedation, and their use tends to be withheld [2]. Moreover, severe postoperative pain can be a risk factor for postoperative chronic pain due to the delay in motor function recovery that inhibits rehabilitation [3]. Anticonvulsants such as pregabalin and various anxiolytics for perioperative anxiety have been tried as measures against postoperative pain, but there are problems such as ineffectiveness and strong side effects.

Yokukansan is a type of Chinese herbal medicine that has been used for night crying, and hysteria in children but recently is used for dementia-associated symptoms [4] and neuropathic pain [5]. Yokukansan is thought to have a reducing effect on excitability and some effect on pain and emotions. The applicant has also been prescribing yokukansan for patients with neuropathic pain or increased pain due to anxiety at an outpatient clinic. A study examining the effects of yokukansan on perioperative anxiety and sedation levels [6] suggests that yokukansan has the effect of suppressing anxiety while minimizing sedation. No clinical studies have been conducted to investigate whether or not it is effective for postoperative pain. We planned this study because we thought that the anxiolytic and analgesic effects of yokukansan might also benefit perioperative patients.

[1] J. K. Carroll E, et al, *British Journal of Nursing*. 2012; 21(8):479-483

[2] P.F. White, B. et al, *Anesthesia and Analgesia*. 2009; 108(4)1140-1145

[3] Patricia R. Pinto, et al, Journal of pain research. 2012;13(11)1045-1057

[4] Matsunaga S, et al, J Altzheimers Dis. 2016;54(2) 635-43

[5] Nakamura Y, et al, Masui. 2009; 58(10) 1248-55

[6] Young-Chang Arai, et al, Evidence based Complementaly and Alternative Medicine.2014; ID965045

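### Pain VAS and QOR are compared without a covariate although pre-dose anxiety scores are collected: a small, nearly free gain in precision is left unused

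*Protocol*

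**What the plan says.** Section 4 ⑥ of the protocol makes salivary amylase primary and then lists "Secondary endpoint: HADS STAI QOR Pain VAS". Section 4 ④ [4] places "visual analog scale of pain: VAS, QOR (Quality of recovery), and the presence or absence of analgesic use 24 hours after surgery", and the schedule table shows no earlier VAS or QOR.

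Section 4 ⑦ names three frequentist methods. Two are "t-tests that do not correspond to continuous variables, Fisher's exact test for scale classification" (the first reads as the unpaired t-test); the third is the "Mann-Whitney U test for continuous variables or ordinal variables that do not follow a normal distribution such as VAS". VAS therefore has a test assigned by name and QOR does not, but all three are two-group tests without covariates. The Bayesian analysis is confined to the primary endpoint and is again a difference between two independent groups. No adjusted model appears anywhere in the protocol.

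Two other places matter. Section 4 ④ [1] requires, for all subjects, that staff "before taking the study drug, record the measurement of amylase in saliva, the Hospital anxiety and depression scale (HADS" and the STAI. Section 3 gives the clinical reasoning that "reducing excessive perioperative anxiety is known to be shortened the postoperative course and hospitalization period and postoperative pain".

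**The concern.** Adjusting an endpoint for its own baseline is possible for amylase, HADS and STAI, but not for pain VAS or QOR, which are first measured after surgery. For these two the obvious pre-treatment predictor is anxiety. The protocol argues that anxiety affects pain and recovery, measures it before dosing in everyone, and then names tests that cannot use it.

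Pain is in the trial's title, and section 3 says that no clinical study has examined yokukansan for postoperative pain, so the VAS comparison is where much of the new information lies. With about 40 patients per group, precision is limited. A covariate chosen after the data of an open-label trial have been seen would carry little weight, so it has to be chosen in advance.

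**Working it through.** **Inputs.** About 40 per group, power 80% and significance level 0.05 ("1-β was 80%, the significance level was 0.05"), intervention success rate 75% and meaningful difference 0.3, all from section 4 ⑤. Assumed, because the documents do not say: a two-sided test, 0.3 read as a difference in success rates (control 45%), and the correlation r between the baseline anxiety score and 24-hour VAS or QOR.

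**The plan's own figure.** For 75% against 45%, the mean rate is 0.60 and

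n = [1.96·√(2·0.60·0.40) + 0.8416·√(0.75·0.25 + 0.45·0.55)]² / 0.30² = (1.358 + 0.555)² / 0.09 ≈ 40.7, that is 41 per group.

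This agrees with about 40. Reading 0.3 as a standardised mean difference would need 175 per group, which does not agree. The 80% power therefore belongs to a success rate; the protocol claims no power for VAS or QOR.

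**Effect of one baseline covariate.** Residual variance is multiplied by 1 − r². The equivalent unadjusted size is 40/(1 − r²). Estimating one covariate costs a factor of about 1 + 1/(2·40 − 4) = 1.013, so the net variance factor is 1.013·(1 − r²).

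| Assumed r | Fall in residual variance | Equivalent per group | Net variance factor |
|---|---|---|---|
| 0.1 | 1% | 40.4 | 1.003 |
| 0.2 | 4% | 41.7 | 0.973 |
| 0.3 | 9% | 44.0 | 0.922 |
| 0.4 | 16% | 47.6 | 0.851 |
| 0.5 | 25% | 53.3 | 0.760 |

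Break-even is where 1.013·(1 − r²) = 1, that is r² = 1/77 and r ≈ 0.11.

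**Chance imbalance.** In units of the baseline SD, the between-group difference in mean baseline anxiety has SD √(2/40) = 0.224. Its effect on the outcome is multiplied by r: at r = 0.3 it is 0.3 × 0.224 ≈ 0.07 outcome SD, against an unadjusted standard error of 0.224 outcome SD. In variance terms that is r² = 9%, the same 9% as in the table. It is the same loss seen from another side, not a second one.

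**Simulation with ranks (illustrative).** Normal data, 40 per group, 4,000 runs per setting. The standardised difference is 0.626, chosen because it gives 80% power for an unadjusted comparison of means (normal approximation); it is not a figure of the protocol.

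| Assumed r | Mann-Whitney power | Rank ANCOVA power |
|---|---|---|
| 0.1 | 76.8% | 76.9% |
| 0.3 | 77.1% | 80.7% |
| 0.5 | 76.5% | 86.1% |

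With no true difference, both methods rejected in about 5% of runs (4.5% to 5.6% over all settings).

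**The case against.** The strongest reply is that an unadjusted Mann-Whitney test on a randomised secondary endpoint is not an error, and that covariates for secondary endpoints are commonly left to the SAP. The first half stands: the simulated error rate is about 5%. The second half carries less weight, because the protocol does not leave the method open; it names tests, and none of them adjusts.

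The size is also uncertain. No correlation is given, and section 3 speaks of reducing excessive anxiety. That makes a pre-operative score a plausible predictor of 24-hour pain or recovery but does not establish it as one. Section 5 (2) excludes patients on anti-anxiety or antipsychotic drugs, which may narrow the range of baseline anxiety and lower the correlation. This stands, and it is why the range has to include the case of no gain.

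A further fair point concerns the covariate itself. The trial is open label, and the questionnaires need only precede the study drug. A patient who already knows the allocation could answer a state-anxiety form differently. This stands as a condition on the fix.

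A reader might also infer that chance differences in anxiety bias the pain result, or that adjustment would lift the trial's power from 80% to some higher figure. The documents support neither. Chance imbalance is already part of the unadjusted test's sampling error, and the stated 80% refers to a success rate, not to VAS or QOR.

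**Conclusion.** The point holds as a missed gain in efficiency on two secondary endpoints. It is not a flaw in validity and does not touch the primary endpoint. For assumed correlations from 0.1 to 0.5 the fall in residual variance runs from 1% to 25%, or about 0.4 to 13 extra patients' worth of information per group. At 0.2 to 0.3 the gain is modest, about 2 to 4 patients per group; below about 0.11 it vanishes. These figures rest on the assumed correlation, on about 40 analysed per group, and on a roughly linear relation (on the rank scale for VAS). Any power figure is illustrative only. For QOR, the statement that no adjustment is planned is inferred from the list of tests, since none is assigned to it by name. Low priority, but worth making because it costs almost nothing.

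**What to change.** Add to section 4 ⑦ that pain VAS and QOR are each compared between groups with one pre-specified baseline anxiety score as the only covariate. The pre-operative STAI score would serve, with the scale to be used named in advance. One score is enough: several overlapping anxiety scores at this sample size would add little.

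- QOR: linear regression on group and the baseline score.
- Pain VAS: rank-based ANCOVA, regressing the ranks of VAS on group and the ranks of the baseline score.
- Sensitivity: the Mann-Whitney test already planned for VAS.

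State in section 4 ④ [1] that the questionnaire is completed before the first dose and before the patient knows the allocation.

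Recording a pre-operative pain VAS or QOR as a further covariate is not recommended. It is extra data collection, and exclusions ③ and ⑦ in section 5 (2) probably leave pre-operative pain near zero.

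The cost is a few lines of analysis wording, one degree of freedom, and attention to the order of questionnaire and allocation. No new measurement is needed.
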